#### Lifestyle guidance

Subjects in both groups of the study will receive dietary and lifestyle advice from a research dietitian. This advice is according to the 2013 National Health and Medical Research Council dietary guidelines for Australian adults. The guidelines focus on improving fruit and vegetable intake, portion size control, reduction of energy-dense and low-nutrient density foods and drinks, encouraging physical activity by walking 10,000 steps per day and reducing sedentary behaviour. At baseline, participants will be provided with a pedometer to track the number of steps they take.

### Outcome measures

#### Primary outcome measure

The difference in any change in fasting plasma glucose level between the intervention and placebo groups between baseline and 12 weeks.

#### Secondary outcome measures

The safety of the probiotic formulaThe change between groups in the following biomarkers or measurements from baseline to 12 weeks:(i)HbA1c(ii)insulin sensitivity indices, including Matsuda-ISI [16] and homeostatic model assessment-IR [17](iii)fasting plasma lipids, such as triglycerides, free fatty acids, total cholesterol, HDL-c and LDL-c(iv)plasma zonulin and lipopolysaccharide(v)hs-CRP(vi)gastrointestinal symptoms(vii)body mass index, waist circumference, and waist and hip ratio(viii)blood pressure(ix)faecal microbial and metabolomics profiles.

### Participant timeline

Screening, intervention and assessment visits will be performed by a research nutritionist. The schedule of visits and measurements is given in Fig. 2 in compliance with SPIRIT guidelines.

**Fig. 2 Fig2:**
[figure not shown]
SPIRIT schedule of enrolment, interventions and assessments

### Data collection

#### Clinical examination

Medical history, prescribed and non-prescribed medications, alcohol intake and smoking habits will be recorded during the screening visit. Anthropometric measurements will be collected using standardized examination procedures [18] and calibrated equipment at three time points (baseline, 6 weeks and 12 weeks). Height will be measured using a stadiometer with an adjustable headpiece. Participants will be weighed wearing an examination gown and underwear only. Waist circumference will be measured at the midpoint between the lowest margin of the last rib and the top of the iliac crest. Hip circumference is measured around the widest portion of the buttocks.

Participants will record a 7 day food diary (5 working days and 2 weekend days) at baseline, then at 6 and 12 weeks after randomization. Food Works 8 will be used to assess energy and macronutrients including dietary fibre intake. Participants will wear a pedometer for the study duration. The Stanford Leisure-Time Activity Categorical Item (L-Cat) 2.2 physical activity questionnaire [19] will be completed at baseline, and 6 weeks and 12 weeks after treatment. The number of steps taken will be recorded daily in a study diary.

#### Blood samples

Blood samples will be collected after fasting overnight at baseline and 12 weeks. Participants who do not have type 2 diabetes mellitus will undergo a 75 g oral glucose tolerance test to assess glucose and insulin levels at three time points (0 min, 60 min and 120 min). Blood samples to measure glucose, insulin, HbA1c, lipids and hs-CRP will be sent to a commercial laboratory for analysis. Samples of 12 ml of blood collected in ethylenediaminetetraacetic acid (EDTA) plasma tubes will be used for lipopolysaccharide and zonulin analysis. These samples will be immediately placed at 4 °C and centrifuged for 15 minutes at 1000 *g* (or 3000 rpm) at 2–8 °C within 30 minutes. Plasma samples will be aliquoted in pyrogen-free tubes using pyrogen-free pipette tips and stored at −80 °C. Serum endotoxin will be measured using the Pierce™ Limulus Amoebocyte Lysate chromogenic endotoxin quantification kit (Thermo Fisher, Sydney, NSW, Australia). The EDTA-plasma zonulin concentration will be measured with the human haptoglobin ELISA kit (Abcam®, Sydney, NSW, Australia). Lipopolysaccharide and zonulin analyses will be performed in duplicate.

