**Methods:**

Sixty adults with a body mass index ≥25 kg/m^2^ with prediabetes or type 2 diabetes mellitus (diagnosed within the previous 12 months) will be enrolled in a double-blind, placebo-controlled pilot study. Participants will be randomized to a multi-species probiotic or placebo for 12 weeks. Both groups will receive lifestyle and nutritional advice. The primary outcome measure is the change between groups in fasting plasma glucose levels from baseline to 12 weeks. Secondary outcome measures include, but are not limited to, the change in lipid profile, systemic inflammation, gut permeability, and faecal microbial and metabolomic profiles. Blood and stool samples are collected at baseline and 12 weeks after treatment.

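### The zonulin outcome is to be measured with a haptoglobin kit not shown to be specific for zonulin, so the reading should not be reported as zonulin or read as gut permeability

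*Protocol article*

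**What the plan says.** Three places in the protocol article bear on this point.

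- **Abstract, Methods.** The secondary outcomes are summarised as "the change in lipid profile, systemic inflammation, gut permeability, and faecal microbial and metabolomic profiles". Systemic inflammation and gut permeability are two separate items in that list.
- **Secondary outcome measures.** Item (iv), compared between groups as change from baseline to week 12, is "plasma zonulin and lipopolysaccharide". hs-CRP is a separate item (v).
- **Blood samples.** EDTA "plasma tubes will be used for lipopolysaccharide and zonulin analysis". For zonulin the instrument is then fixed: "The EDTA-plasma zonulin concentration will be measured with the human haptoglobin ELISA kit". A separate chromogenic endotoxin kit is named for lipopolysaccharide. The only quality step given for these two assays is this: "Lipopolysaccharide and zonulin analyses will be performed in duplicate".

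Haptoglobin appears nowhere else in the article.

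**The concern.** The outcome carries the name of one analyte and the instrument the name of another. If the plan is followed as written, a reading from a haptoglobin kit will be tabulated as a zonulin concentration.

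This matters because of what the outcome is there to show. No other item on the secondary list fits the gut-permeability domain as naturally as zonulin and lipopolysaccharide. The Background hypothesises that the probiotic will lower inflammatory markers. As general biochemistry, circulating haptoglobin also varies with inflammation. If the kit reads total haptoglobin, an anti-inflammatory effect alone could lower the reading, and that fall could be taken as better barrier function. Two domains that the abstract keeps apart would then be mixed, in the direction that favours the trial's proposed mechanism.

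**Working it through.** No figure in the plan is in dispute, so there is nothing to reproduce. The check sets the text on the outcome beside the text on the instrument.

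**1. Label against instrument.**

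| Element | What the article gives | Where |
|---|---|---|
| Domain | Gut permeability, separate from systemic inflammation | Abstract, Methods |
| Outcome | Plasma zonulin, item (iv) | Secondary outcome measures |
| Sample | EDTA plasma, aliquoted and stored at −80 °C | Blood samples |
| Instrument | Human haptoglobin ELISA | Blood samples |
| Quality step | Duplicate measurement | Blood samples |
| Statement linking haptoglobin to zonulin | None | – |

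**2. Does anything bridge the gap?** Three kinds of sentence could do so: that the kit detects zonulin specifically, that haptoglobin is used deliberately as a surrogate, or that specificity was validated. The article has none of them. Duplicates address repeatability. They do not show which molecule is being read, since two concordant wells can both be reading haptoglobin.

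**3. Is zonulin the permeability measure?** The article does not say so outright. It is an inference from reading the abstract's list against the detailed list. Lipids, hs-CRP and the faecal profiles account for the other domains named in the abstract, which leaves item (iv) as the natural carrier of gut permeability.

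**4. How many readings?** Planned enrolment is 60, with sampling at baseline and week 12, so at most 60 × 2 = 120 readings. The Sample size section allows for 25% drop-out: 0.25 × 60 = 15 participants. If all 15 lacked a week-12 sample, 60 + 45 = 105 readings would be measured. The remaining 15 would be filled with baseline values under the rule in Statistical analysis. The labelling problem applies to every reading in either case.

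**5. What else depends on it?** The primary outcome is fasting plasma glucose, and the sample size is built on that variable. Neither uses the zonulin assay. Lipopolysaccharide, the other half of item (iv), has its own kit.

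**The case against.** The strongest reply is that zonulin is itself described as a haptoglobin precursor, so a haptoglobin kit may detect it and may have been chosen for that reason. The article gives no information on what the kit's antibodies bind. A reader might infer that the trial will certainly report an inflammation protein and will not measure zonulin at all. The documents do not support that: some detection of zonulin cannot be excluded. What they support is narrower, namely that specificity is not shown. Cross-detection would not rescue the label, because a signal combining zonulin with other haptoglobin is still not a zonulin concentration.

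A second reply is that a journal article condenses, and assay validation may sit in the full protocol or a laboratory manual. That is fair as far as missing validation detail goes. But the article positively states both the outcome name and the instrument, and the two do not match. If evidence of specificity exists elsewhere, citing it would resolve the point.

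A third reply is that no sentence commits the investigators to calling a fall in the reading improved permeability. That is correct. The risk comes from the outcome's name and the domain it naturally serves, not from a stated reporting rule.

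Finally, lipopolysaccharide and hs-CRP are measured separately, so a parallel inflammatory change could be examined and the barrier question does not rest on zonulin alone. This stands, and it limits the point to one of the two markers in item (iv).

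**Conclusion.** The point holds as a mismatch between outcome and assay. As the text stands, the reading may reflect total haptoglobin, so it should not be reported as a zonulin concentration or interpreted as a permeability marker without justification.

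Its reach is one secondary outcome in a pilot trial: all of that outcome's readings, and nothing in the primary analysis or sample size. It should be corrected, but it does not threaten the trial's main result.

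The conclusion rests on the article's own wording and on one piece of general biochemistry, that haptoglobin varies with inflammation. It assumes nothing about this kit's cross-reactivity. A reader might go further and infer that a true change in zonulin would be invisible in the result, or that no conclusion about the barrier would be possible. The first would need the concentrations of both proteins and the kit's binding properties, none of which the article gives. The second overlooks the separate lipopolysaccharide measurement.

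**What to change.** Take one of two routes before the results are reported. Trial status describes recruitment as ongoing at the time of writing.

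1. **Keep the outcome and justify or change the assay.** Under Blood samples, name an assay shown to be specific for zonulin, cite the evidence, and run it on the EDTA plasma held at −80 °C. The cost is a possible change of kit; no extra visit or sample is needed. This route is open only if such specificity can be demonstrated, and the article cannot settle whether it can.
2. **Keep the kit and change the outcome.** Relabel item (iv) as plasma haptoglobin and lipopolysaccharide, make the same change under Blood samples, and state that no gut-permeability conclusion will be drawn from haptoglobin. This is a wording change. Its cost is the loss of one permeability marker, with lipopolysaccharide remaining.

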#### Stool samples

Stool samples will be collected at baseline and 12 weeks using a stool specimen collection kit. This collection kit includes an instruction booklet for the stool sample collection and transportation, ice packs, gloves, a sterile container, sealed plastic pouch, cool box and an AnaeroGen™ Compact sachet, which preserves the microbiological characteristics of the sample for 72 hours. Participants will bring the stool sample to the clinic and the containers will be stored at 4 °C and analyzed by matrix-assisted laser desorption ionization time-of-flight mass spectrometry 24–48 hours after collection. In addition, a 1 g sample will be stored at −80 °C for faecal microbial and metabolite profiling. DNA extraction will be performed using the QIAamp DNA stool kit (Qiagen, Sydney, NSW, Australia). Faecal microbial composition will be identified by sequencing the 16S rRNA using the Ion S5 next-generation sequencing system (Thermo Fisher, Sydney, NSW, Australia). Short-chain fatty acids, secondary bile acids and choline by-products will be measured using gas chromatography-mass spectrometry.

### Data analysis and statistical considerations

#### Sample size

As this is a pilot study, no evidence about blood glucose differences is available for this product. Therefore, it was decided to use the number of participants needed to detect a mean difference between the groups in fasting plasma glucose level of 2.0 mmol/l (standard deviation 2.0 mmol/l) at week 12 with 80% power and 95% confidence as a starting point. The number of subjects needed is 32. The fact that the study includes two different cohorts (participants with prediabetes and early type 2 diabetes mellitus) was also taken into consideration, as owing to the lack of stratification at randomization the variance could be high. Therefore, the sample size has been inflated to 30 per group (including a drop-out rate of 25%) to give a total sample size of 60 eligible participants.

#### Statistical analysis

Analysis will be conducted using the intention-to-treat principle and missing data will be imputed with baseline values for a conservative estimate (i.e. no change). Descriptive statistics will be presented as mean ± standard deviation, or median with range, as appropriate. Primary and secondary outcomes will be analyzed using generalized linear models. The following covariates will be added to the model: sex, age and percentage weight change. Additionally, if there is an imbalance between the groups of prediabetes and type 2 diabetes mellitus, this will be included as a covariate in the model. Three planned subgroup analyses will be completed between participants who are taking metformin, participants classified as prediabetic or type 2 diabetes mellitus and participants defined as compliant. Chi–square analysis will determine associations between categorical variables.

For the gut microbiome analysis, sequenced data will be interpreted using the bioinformatics tools programmed in the Ion Reporter™ software. Quantitative Insights Into Microbial Ecology (QIIME) algorithms will determine the bacterial diversity within a sample (alpha diversity) and between all the samples (beta diversity). Additionally, multivariate data analysis with principal component analysis on the diversity indexes and comparisons of genus and species level data will be performed to reveal differences in the microbial composition between the two groups. Differences in relative abundance of taxa between the intervention and placebo group and between participants receiving and not receiving metformin will be determined using ANOVA, using subject as a blocking factor. Changes in relative abundance will be tested for correlations with patient biochemical measurements. For all statistical tests, the Benjamini–Hochberg false discovery rate adjustment [20] will be used to account for the number of taxa tested in each comparison.

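### Setting missing week-12 values to baseline is conservative only if drop-out is equal between arms and unrelated to outcome, and even then it distorts the pilot's effect estimate and SD

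*Protocol article*

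**What the plan says.** The Statistical analysis section sets the principle, "Analysis will be conducted using the intention-to-treat principle", and then the rule and its justification: "missing data will be imputed with baseline values for a conservative estimate (i.e. no change"). The rule is worded generally, so it covers the secondary outcomes as well as the primary one. The article names no other missing-data method.

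The primary outcome is "The difference in any change in fasting plasma glucose level between the intervention and placebo groups between baseline and 12 weeks". The Blood samples section schedules fasting blood at baseline and week 12 only. A participant without the week-12 sample therefore has no post-baseline glucose and receives a change of exactly zero.

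The Sample size section takes a difference in "fasting plasma glucose level of 2.0 mmol/l (standard deviation 2.0 mmol/l) at week 12", "with 80% power and 95% confidence as a starting point", and reaches 60 participants, "including a drop-out rate of 25" per cent. Under Lifestyle guidance, "Subjects in both groups of the study will receive dietary and lifestyle advice from a research dietitian".

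**The concern.** At the planned drop-out rate, 0.25 × 60 = 15 of the 60 primary-outcome values would be constructed. Each arm's mean change is multiplied by one minus that arm's drop-out rate. Both arms receive advice that could lower glucose, so a non-zero change on placebo is plausible. If the arms then lose different numbers of people, their means shrink by different amounts and a difference appears where there is none. Its direction depends on which arm loses more.

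With equal losses a real difference is still reduced. The Discussion presents the trial as a source of pilot data, and the effect size and the SD are what a pilot passes to the next study. This rule alters both.

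**Working it through.** **Inputs from the Sample size section:** difference 2.0 mmol/l, SD 2.0, 80% power, 95% confidence (read as two-sided alpha 0.05), 30 per arm, 25% drop-out.

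**Assumptions:** the SD of 2.0 is used as the SD of change, although the plan ties it to week 12. Arm-specific drop-out rates and the common change are not in the document and are shown as ranges. The simulations use an unadjusted two-sample t-test on change, with drop-out unrelated to outcome.

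**1. The plan's figure.** n per arm = 2 × (1.96 + 0.84)² × 2.0² / 2.0² = 15.7, so 16 per arm and 32 in total. This agrees with the plan. After 25% drop-out, 60 enrolled leaves 45 completers, or 22.5 per arm on average.

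**2. Formulas.** For true mean change μ, SD σ and drop-out fraction d, after imputation:
- mean = (1 − d)μ
- SD = √[(1 − d)σ² + d(1 − d)μ²]

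**3. Equal 25% drop-out, μ = −2 on probiotic and 0 on placebo.**
- Expected difference = 0.75 × (−2) = −1.5.
- SD on placebo = √(0.75 × 4) = 1.73. SD on probiotic = √(3 + 0.1875 × 4) = 1.94. Pooled SD = 1.84.
- The SD is understated while |μ| is below σ/√(1 − d) = 2.0/√0.75 = 2.31, which includes the planned effect.
- SE = 1.84 × √(2/30) = 0.474. The interval is centred 0.5/0.474 = 1.05 SEs from the truth, so coverage of 2.0 is about Φ(1.96 − 1.05) − Φ(−1.96 − 1.05) ≈ 0.82. Simulation gives 81–82%.
- Analysing completers only gives an estimate of 2.00. Power is about 88% with imputation and about 90% with completers.

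**4. Unequal drop-out, no true effect, common change m.** Difference (probiotic minus placebo) = (d_placebo − d_probiotic) × m. Simulated two-sided type I error is at the plan's SD of 2.0, with 30 per arm and 100,000 runs.

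| Drop-out, probiotic / placebo | m (mmol/l) | False difference | Type I error |
|---|---|---|---|
| 25% / 25% | 0 | 0 | 5.0% |
| 15% / 35% | −0.5 | −0.10 | 5.8% |
| 15% / 35% | −1.0 | −0.20 | 7.4% |
| 35% / 15% | −1.0 | +0.20 | 7.3% |
| 10% / 40% | −1.0 | −0.30 | 10.2% |
| 35% / 15% | +1.0 | −0.20 | 7.3% |

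A negative difference favours the probiotic. In the last row both arms worsen, and the arm losing more people looks better. A completers-only analysis of the third row gives a mean difference of 0.01 and a rejection rate of 4.85%. Repeat runs put the second and third rows at 5.4–5.8% and 7.0–7.4%.

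**5. Drop-outs who would have worsened.** Suppose completers do not change, drop-outs would have risen by 1.5 mmol/l, and drop-out is 35% on probiotic and 15% on placebo. The true difference is (0.35 − 0.15) × 1.5 = +0.30 against the probiotic. The imputed difference is 0.

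**The case against.** The strongest defence is that the rule behaves as claimed in the simplest case. With equal drop-out unrelated to outcome, the effect shrinks toward zero and type I error stays near 5%. The loss of power at the planned effect is about two percentage points, in a pilot of 60. Glucose is measured once after baseline, so no method recovers much from those who leave. An analysis plan that is not shown may add sensitivity analyses. All of this stands. It limits the point but does not remove it, because equal and non-informative drop-out cannot be guaranteed, and the article gives its justification without that condition.

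Three stronger readings are tempting and are not supported.

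- *The standard error is false because imputed zeros count as data.* With equal drop-out, the reported SE matches the true sampling SD of the imputed-data estimate (0.472 against 0.475 in simulation at the planned effect). The poor coverage comes from attenuation.
- *Type I error reaches 13%.* With 15% against 35% drop-out and falls of 0.5–1.0 mmol/l, a range of 7–13% requires an SD of 1.0. The plan states 2.0, where the figure is about 6–7%. With 20% against 30% drop-out at SD 2.0, it is 4.9% to 5.6%.
- *A follow-on trial would be 25% too small.* The ratio (1.73/2.0)² = 0.75 uses the SD alone, with no mean change. Using the attenuated effect as well gives (1.84/1.5)² ≈ 1.5 against (2.0/2.0)² = 1, so the later trial would be too large. The distortion is real, but its direction depends on which outputs are carried forward.

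A reader might also infer that week-12 blood will not be sought from people who stop the product. The article speaks of discontinuing the product after certain serious adverse events. It does not say that follow-up ends.

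**Conclusion.** The point holds in a limited form. Calling baseline imputation conservative is correct only when drop-out is equal between arms and unrelated to outcome. Even then, at the plan's own inputs, a true 2.0 mmol/l is estimated as 1.5, the interval covers the truth about 81–82% of the time, and the SD of change is too small (1.73 where mean change is zero, 1.94 where it is −2).

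If drop-out differs and both arms change, the estimate can be biased toward either arm: 0.10–0.20 mmol/l, with type I error about 6–7%, under the assumed 15%/35% drop-out and common fall of 0.5–1.0 mmol/l at SD 2.0. If drop-outs would have worsened, the rule conceals it.

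The attenuation and SD figures rest on the plan's inputs, with its SD read as the SD of change. The unequal-drop-out figures rest on assumed rates and changes. The error-rate inflation is modest, so the main cost is a biased effect estimate and a distorted SD from a trial meant to inform the next one.

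**What to change.** Make the primary analysis one that is valid under missing at random: week-12 fasting glucose, adjusted for baseline glucose and diabetes cohort. Use either an observed-data ANCOVA or multiple imputation with a small set of baseline predictors. With about 22 completers per arm, a long list of predictors is not supportable, and week-6 measurements exist only for those who attend that visit.

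Keep baseline imputation as one sensitivity analysis. Add a delta-adjusted one, so that the possibility of drop-outs having worsened is examined openly. Report the SD of change from observed values, and delete the word conservative.

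The change costs some wording and a little code, and the article's Trial status section reports recruitment as still ongoing. The confidence interval will be somewhat wider. Where mean change is zero, the SE is 2.0 × √(2/22.5) = 0.60 with completers, against 1.73 × √(2/30) = 0.45 with imputation. With only one post-baseline glucose value, a missing-at-random analysis removes the systematic pull toward zero but recovers little information about those who leave.

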## Background

The relationship between the gastrointestinal microbiota and obesity-associated disorders has gained extensive research interest in the past 10 years. A disturbed gut microbiota expressed as gut dysbiosis (an intestinal physical barrier abnormality) has been associated with the progression and maintenance of obesity, type 2 diabetes mellitus, cardiovascular diseases and metabolic syndrome [1–5]. The mechanisms by which gut dysbiosis produces and influences these metabolic alterations are via regulation of the host’s energy balance and storage and by promoting endotoxaemia or bacteraemia [6]. Furthermore, postprandial blood glucose levels are very much influenced by the gut bacteria, with recent research demonstrating a profound influence on how individuals responded to identical food items that could be accurately predicted based on their gut bacterial profiles [7]. Gut dysbiosis may be restored to a balanced state through microbiota-based interventions, which may improve metabolic markers associated with type 2 diabetes mellitus through immunomodulatory and anti-inflammatory pathways.

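### Percentage weight change, known only after randomisation, is a covariate in the primary and secondary outcome models: it cancels the BMI comparison and may remove part of the glucose effect

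*Protocol article*

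**What the plan says.** The Statistical analysis section of the protocol article states: "Primary and secondary outcomes will be analyzed using generalized linear models". The next sentence sets the covariates: "The following covariates will be added to the model: sex, age and percentage weight change". The adjustment is unconditional. No model without weight change is described, and the adjusted model is not labelled a mediation or sensitivity analysis.

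The same section opens with: "Analysis will be conducted using the intention-to-treat principle and missing data will be imputed with baseline values for a conservative estimate".

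The primary outcome is: "The difference in any change in fasting plasma glucose level between the intervention and placebo groups between baseline and 12 weeks". The secondary outcomes include changes in "body mass index, waist circumference, and waist and hip ratio".

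Under Clinical examination, anthropometry is taken with "calibrated equipment at three time points (baseline, 6 weeks and 12 weeks"), so percentage weight change cannot be known at randomisation. The article does not name the interval; I take it to be baseline to 12 weeks, matching the outcomes.

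The Background says gut dysbiosis acts on metabolism "via regulation of the host’s energy balance and storage and by promoting endotoxaemia or bacteraemia". It also reports that, in vitro, culture supernatants of this formula reduced fat accumulation in an adipocyte line.

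**The concern.** A covariate that treatment can alter changes what the treatment coefficient means. The primary outcome is a total effect: how much glucose change differs between arms, by whatever route. Holding weight change fixed leaves, at best, the part of that difference that does not run through weight.

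Two things are at stake.

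- **BMI.** The covariate and the outcome carry almost the same information, so the model cannot detect an effect on BMI even if there is a large one. Waist and waist/hip move with weight and are affected in part.
- **Glucose.** If the product lowers weight and weight lowers glucose, a real benefit is under-reported in the primary analysis. In addition, diet and activity can drive both weight and glucose and are not in the model. Comparing participants with equal weight change can then compare people who differ in diet and activity, which biases the estimate. The direction depends on the sign of the product's effect on weight and on how diet and activity relate to both variables.

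**Working it through.** **1. The plan's own figure.** Sample size section: difference 2.0 mmol/l, SD 2.0 mmol/l, 80% power, 95% confidence (taken as two-sided 5%). Per arm, n = 2 × (1.960 + 0.842)² × (2.0/2.0)² = 15.7, rounded up to 16, or 32 in total. This matches the stated 32. The final size is 30 per arm. The sample size arithmetic is not at issue; it supplies the inputs below.

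**2. BMI, by algebra.** With height fixed, percentage change in BMI equals percentage change in weight, p. In absolute units:

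change in BMI = B0 × p/100 = B̄ × p/100 + (B0 − B̄) × p/100,

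where B0 is baseline BMI and B̄ its mean. The covariate p absorbs the first term. The second averages to zero in both arms, because randomisation balances B0 and provided B0 is unrelated to p. Treatment has nothing systematic left to explain. Setting missing weights to baseline does not alter this: both sides are then zero.

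Simulation check: 30 per arm, 4,000 runs per scenario, linear model with treatment, sex and age, with and without p. Assumptions: SD of p 3 percentage points; baseline BMI mean 32, SD 5, floored at 25.

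| Assumed weight effect (points) | BMI difference without p (kg/m²) | Rejection without p | BMI difference with p | Rejection with p |
|---|---|---|---|---|
| −1 | −0.33 | 24% | 0.00 | 4% |
| −2 | −0.64 | 69% | 0.00 | 4% |
| −3 | −0.96 | 95% | 0.00 | 3% |

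**3. Glucose, by assumed share acting through weight.** The documents give no figure, so the share s is an assumption. Adjusted effect = 2.0 × (1 − s). Standard error at 30 per arm = 2.0 × √(2/30) = 0.516. Power = Φ(effect/SE − 1.96), holding the SD at 2.0. With 25% drop-out, 30 × 0.75 leaves about 22 per arm (SE 0.603).

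| Share s | Adjusted effect (mmol/l) | Power, 30 per arm | Power, 22 per arm |
|---|---|---|---|
| 0% | 2.0 | 97% | 91% |
| 10% | 1.8 | 94% | 85% |
| 25% | 1.5 | 83% | 70% |
| 50% | 1.0 | 49% | 38% |

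Example for s = 25%: 1.5/0.516 − 1.96 = 0.95, and Φ(0.95) is about 0.83.

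**4. Glucose, by assumed weight effect and slope.** With d the effect on weight in points and b the glucose slope per 1% weight, adjusted effect = total − b × d. For a total of −2.0, b = 0.3 and d = −1, −2, −3, this gives −1.7, −1.4 and −1.1. The simulation, which also lets the residual variance and the treatment–weight correlation change, gave −1.69, −1.41 and −1.10. Power was 94%, 79% and 53%, against about 96% without p. With b = 0.5 and d = −3 the estimate was −0.51 and power 25%. With d = 0 the estimate stayed at −2.0, and power was 99% with p against 97% without. These runs contain no shared cause of weight and glucose; they restate the formula and add the power.

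**The case against.** The strongest case for the plan is that both arms receive diet and activity advice, so weight will change for reasons unrelated to the product. Removing that variation sharpens the glucose comparison, and if the product does not affect weight the adjusted model is unbiased and slightly more powerful. The Background passage on energy balance describes how dysbiosis acts. For microbiota-based treatment it names immune and inflammatory routes, and the hypothesis does not mention weight loss. The study is also a pilot.

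Part of this stands. It explains the choice, and it makes the glucose loss conditional. It does not rescue BMI, and the primary analysis should not depend on the product leaving weight unchanged when measures of body size are listed as outcomes. Randomisation already balances the effect of lifestyle advice in expectation. The article names a primary efficacy outcome and gives a power calculation, so the quantity estimated matters even in a pilot.

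A reader might infer several stronger claims that the article does not support:

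- **That every outcome is affected.** Taxa are compared by ANOVA, and adverse events are reported descriptively.
- **That intention-to-treat is abandoned.** Participants are still analysed as randomised. What changes is the effect being estimated.
- **That diet and activity are unmeasured.** Food diaries, daily step counts and an activity questionnaire are collected; they are simply not in the model.
- **That false-positive findings of benefit become common.** The strength of any shared cause is unknown. As illustration, an assumed bias of +0.25 mmol/l at SD 2.0 and 30 per arm is 0.25/0.516 = 0.48 standard errors, giving about 7% to 8% rejection instead of 5%, and its sign would suggest harm. This bias, too, needs the product to shift weight.

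**Conclusion.** The analysis is wrong as written. For BMI the conclusion follows from algebra and needs no assumption about effect size: the specified model returns a treatment effect of about zero whatever the truth. Waist and waist/hip are distorted in part, by an amount the documents do not allow one to calculate.

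For fasting plasma glucose, the model does not target the total between-arm difference named as the primary outcome. Whether this costs anything depends on a product effect on weight. The Background and the list of secondary outcomes make that plausible, but no size is given. Across an assumed mediated share of 10% to 50%, the estimate falls from 2.0 to between 1.8 and 1.0 mmol/l, and power at 30 per arm from 97% to between 94% and 49%. With no weight effect there is no attenuation. It would therefore go too far to say that the model certainly removes part of the glucose effect.

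A fuller analysis plan may exist. It would have to reverse the stated sentence, not merely add detail, to cure this.

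**What to change.** Delete percentage weight change from the models for the primary and secondary outcomes and adjust for baseline variables only: sex, age and, for precision, the baseline value of the outcome.

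If the role of weight is of interest, report a weight-adjusted glucose model separately, labelled as an exploratory mediation analysis, with the assumption about shared causes such as diet and activity stated. Do not use such a model for BMI, waist or waist/hip.

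The cost is one sentence in the analysis section and some loss of residual-variance reduction. In the simulation with no weight effect and a slope of 0.3 mmol/l per 1%, that loss was about 2 percentage points of power (99% to 97%). Adjusting for baseline glucose may recover some of it, but the documents give no figure from which to say how much.
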